##### Data Monitoring Committee

Independent of the investigators and midwives who include participants, there will be one obstetrician and one midwife, both experienced and clinically active who will monitor the study. As a first step, they will monitor (1) eligibility to the study and (2) protocol adherence blinded for primary outcome, second, when this is done, they will monitor the primary outcomes.

##### Statistical analyses of data

We will report data both as intention to treat and as per protocol. Per protocol data results will be considered as the clinically relevant, as the study is based on two different protocols for management of labour. The statistical program IBM SPSS Statistics for Windows version 25 will be used (IBM Corp., Armonk, NY, USA). We will report missing data as missing data. No imputation will be made.

Differences between categorical variables will be analysed by Pearson chi-square test.

*P* values < 0.05 are considered statistically significant. Continuous variables will be analysed by odds ratio and standard mean differences. Confidence intervals will be reported.

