### Study hypotheses

H^0^: Women randomized to proactive labour support versus those randomized to standard labour support have similar rate of normal deliveries.

H^0^: Women randomized to proactive labour support versus those randomized to standard labour support have no difference in birth experience.

H^1^: Women randomized to proactive labour support have a higher rate of normal deliveries compared to those in the standard labour support group.

H^2^: Women randomized to proactive labour support have better birth experience compared to those in the standard labour support group.

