### Study design

The present study is an open-label RCT with randomization to proactive support or standard support during labour. Women will be informed about the study at gestational week 18, and reminded at week 36/37, at an outpatient consultation. Women who meet the inclusion criteria will be included in the study and randomized at arrival to the delivery department.

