### Repeated information to colleagues

Evaluation after 1 year of inclusions has revealed major challenges that needed to be addressed. Dialogue with the midwives in the maternity ward revealed a gatekeeper effect due to midwives’ limited motivation to recruit, and include, women to the study. The midwives’ questions and concerns were collected and reviewed thoroughly by the research group. Concerns and limited motivation were due to the fear of unnecessary interventions such as amniotomy, oxytocin use and an overall aim of a “natural delivery”. Midwives in the delivery department were concerned that the evaluation after 12 hours for instrumental delivery might lead to an increased rate of caesarean section. A subsequent explanatory information letter was distributed individually to all midwives. In addition, the questions and concerns were discussed with the midwife group. The written form and the flow chart were adjusted to avoid misinterpretations. Consequently, more women were included in the study.

Concerns about lack of evidence-based practice, were not expressed. Motivation in the midwife group increased with improved information and dialogue. The quality of the study is dependent on the midwives’ compliance to the flow chart during labour for the intervention group.

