### Blinding

Blinding is not possible in such a RCT-study. A spillover effect might be expected. Midwives care for women in both the intervention group and in the control group. This might affect the result, based on the midwife’s experiences when she follows the two different procedures. We realize that it might be a challenge for the midwives to follow up labour according to two different “protocols”. The spillover effect is expected to be limited and not expected to reduce the validity of the study.

The standard care depends on the capacity at the delivery department, the midwife’s assessment and the woman’s capability to ask for what she needs. Women randomized to the control group are not always asked to return home if they are exhausted or live far away. These women might stay in the ward and are especially prone to a spillover effect. This might mask differences between standard care and the intervention care.

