### Trial status

The study is currently recruiting participants. Since study start in April 2017 and through May 2019, 90 eligible women have been included in the study. Two women were excluded due to undetected breech presentation and one due to assumption of a vasa previa. Two were included on the wrong premises. Four were randomized to the intervention group, but the midwife did not follow the protocol. One woman wanted to leave the study after inclusion. The estimated time for end of inclusion will be December 2020.

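### Per-protocol results are given priority over intention to treat in an open-label superiority trial, leaving the main comparison open to bias of unknown size and direction

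*Protocol article*

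**What the plan says.** The section on statistical analyses of data in the protocol article commits to both analyses: "We will report data both as intention to treat and as per protocol". It then ranks them: "Per protocol data results will be considered as the clinically relevant, as the study is based on two different protocols for management of labour". ITT is not named as primary anywhere in the article.

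The setting in which that ranking applies is as follows.

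- The hypothesis is superiority: "Women randomized to proactive labour support have a higher rate of normal deliveries compared to those in the standard labour support group". No non-inferiority margin is given.
- Nobody on the ward is blinded: "The present study is an open-label RCT with randomization to proactive support or standard support during labour".
- Under Repeated information to colleagues, the article reports that midwives were reluctant to recruit because they feared unnecessary intervention. It adds: "The quality of the study is dependent on the midwives’ compliance to the flow chart during labour for the intervention group".
- Trial status reports departures in one named arm: "Four were randomized to the intervention group, but the midwife did not follow the protocol".
- Under Blinding, control care is described as flexible: "Women randomized to the control group are not always asked to return home if they are exhausted or live far away".
- The Data Monitoring Committee section provides for an obstetrician and a midwife, independent of those who include participants. They review eligibility and adherence without knowledge of the primary outcome, before they look at outcomes.

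**The concern.** In a superiority trial, the analysis that keeps every randomised woman in her allocated arm is the one that randomisation protects. A per-protocol set is formed by what happens afterwards. Here that means a midwife who knows the allocation, is watching the labour, and either follows the flow chart or leaves it. If that choice is related to how the labour is going, or to which women seem unsuited to early intervention, it is also related to whether the birth will count as normal. Removing those women then changes the event rate in their arm for reasons other than treatment.

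The reason given for the ranking is that two management protocols are being compared. That does not support it, since a randomised comparison of two management policies is what ITT estimates. The article's later statement that the randomised design minimises confounding does not carry over to a per-protocol set.

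At stake is the main conclusion. If the two analyses disagree, the plan has already said which one counts.

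**Working it through.** **1. The plan's own figure.** The power calculation gives 30% pathological births in controls, a 50% reduction (to 15%), 80% power and 120 per group. The analysis section gives the significance level: P "values < 0.05 are considered statistically significant". I take the test as two-sided, which is not stated. With pooled variance and mean rate p̄ = 0.225:

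n = [1.960·√(2·0.225·0.775) + 0.842·√(0.30·0.70 + 0.15·0.85)]² / 0.15² ≈ 120.5, so 121 per arm.

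Power at 120 per arm is 79.8%. The stated 120 reproduces, and the sample size is not in error on its own inputs.

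**2. Share removed.** Trial status gives 90 women included and four departures in the proactive arm. Arm sizes are not given. Assuming 45 per arm, d = 4/45 = 8.9%. At full size that is 120 × 0.089 ≈ 11 women, leaving 109 in the proactive arm against 120 controls.

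**3. Per-protocol rate with no true effect.** Let both arms have a true rate of 30%, and let q be the pathological-birth rate among the removed women. The article does not give q, so I vary it. The per-protocol proactive rate is

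p = (0.30 − d·q) / (1 − d).

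Example: q = 0.60 gives (0.30 − 0.0533) / 0.9111 = 27.1%.

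**4. Chance of false significance.** Exact binomial enumeration of the two-sided 5% Pearson chi-square test, 109 v 120, control rate 30%:

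| q among removed women | Per-protocol proactive rate | Significant, favouring proactive |
|---|---|---|
| 0% | 32.9% | 0.8% |
| 30% | 30.0% | 2.5% |
| 50% | 28.0% | 5.1% |
| 60% | 27.1% | 7.1% |
| 80% | 25.1% | 12.8% |
| 100% | 23.2% | 21.3% |

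At q = 30% there is no bias. Above it, the comparison tilts towards proactive support: by 2.9 points at q = 60% and 6.8 points at q = 100%. Below it, the tilt reverses. At q = 0% the chance of a significant result against proactive support is 6.5%.

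**5. What ITT costs in power.** Assume the planned effect (15%) in adherent proactive women and the control rate (30%) in non-adherent ones. The proactive rate becomes 0.15 × 0.911 + 0.30 × 0.089 = 16.3%. Power at 120 per arm is then 71.1% by the normal approximation and about 72% by exact enumeration. Restoring 80% under that assumption would take 149 per arm.

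**The case against.** Several points on the other side have force.

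- **ITT is not withheld.** Both analyses will be reported, and the article does not say that the hypothesis test rests on per-protocol. A reader might infer that per-protocol alone decides the trial, but the text goes only as far as interpretive priority. That priority still lets a favourable per-protocol result outweigh a null ITT result.
- **Adherence is reviewed blind to the primary outcome.** This is a real safeguard, because it keeps the classification from being steered by the result. It does not reach the earlier step, in which the midwife departs from protocol during labour for reasons that may also bear on the outcome.
- **One-sided removal is not established.** A reader might infer that women are lost almost only from the proactive arm. The evidence is four women. Trial status lists six others (two breech, one assumed vasa previa, two included on wrong premises, one withdrawal) without giving their arm, and it does not say that the four will be dropped. Under Interventions, the control arm also has rules that could be broken, such as the longest interval between assessments. The flow charts are not visible.
- **The direction is open.** A reader might infer that the comparison is biased in favour of proactive support. The midwives' stated motives, avoiding intervention and preserving a natural birth, fit leaving the flow chart in labours that are going well at least as readily. That would bias the comparison against proactive support.

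**Conclusion.** The point holds in this form: the plan gives interpretive priority to an analysis that randomisation does not protect, in an unblinded superiority trial, with the known departures all in one arm. The documents support *open to bias*; they do not show that the comparison *is biased*, nor in which direction.

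Under the illustration above, the chance of false significance favouring proactive support runs from 0.8% to 21.3%, against 2.5% when departure is unrelated to outcome. The range rests on three assumptions: equal arms among the first 90 women, removal from the proactive arm only, and an 8.9% share that persists to full enrolment. Not knowing the sign is no defence of the ranking; it is a reason not to base the conclusion on this set.

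**What to change.** In the section on statistical analyses of data, replace the sentence that gives per-protocol priority. Name ITT as the primary analysis and the basis for the conclusion, with all consenting randomised women analysed in their allocated arm, including those whose midwife left the flow chart. Keep per-protocol as a labelled supportive analysis, with its set defined by the outcome-blinded review already described in the Data Monitoring Committee section. A complier-average estimate is optional if the effect under adherence is of interest, since it keeps the randomised groups.

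The change is one of wording and does not itself require more women. Its cost is that ITT may be diluted by non-adherence, and the power calculation shows no allowance for this. The plan should state that power at 120 per arm would be about 71–72% rather than 80% if 8.9% of the proactive arm is non-adherent and has the control rate. The article describes recruitment as still under way, with 90 of the planned 240 women included, so at that point the ranking could still be changed before any analysis.

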### Primary outcome

The primary outcomes of the present study are (1) the rate of normal deliveries and (2) the birth experience measured by the CEQ questionnaire.

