### Assignment of interventions and collection

Written information with a consent form is given to all nulliparous women during pregnancy. When they have signed consent, these women may be included in the study at birth if they fulfil inclusion criteria.

Randomization is open, (not blinded). Randomization is computer-based, supported from the Unit for Applied Clinical Research at the Norwegian University of Science and Technology (NTNU). At randomization, the women are stratified according to body mass index (BMI), because obesity influences almost all aspects of pregnancy and labour. The groups are stratified according to first trimester BMI: BMI < 25, BMI 25–30 or BMI > 30.

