### Continuous midwife support

According to previous research, women with continuous support during childbirth are more likely to have a spontaneous vaginal birth, less likely to have intrapartum analgesics and less likely to report dissatisfaction [14].

In 2015, at St. Olav’s Hospital, a clinical study in the delivery department explored the midwife’s presence on the labour room during active labour. This study found higher maternal satisfaction with the midwife’s presence, and the findings changed the way midwives work at the department. It is now more common that the midwife stays in the labour room during the entire active labour and gives one-to-one support. This is one of the important principles for the proactive support of labour.

The strengths of this present study are many, particularly the randomized, controlled clinical study design. This design minimizes the chance for confounding. The women are also stratified according to BMI to minimize the risk of uneven randomization. RCT is the gold standard for studying causality, which is the objective of this study.

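### Randomisation is stratified by BMI but the stated test for the primary binary outcome ignores the strata: a small, avoidable loss of efficiency, with validity kept

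*Protocol article*

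**What the plan says.** Under Assignment of interventions and collection, the article says that "the women are stratified according to body mass index (BMI), because obesity influences almost all aspects of pregnancy and labour", and sets three classes: "The groups are stratified according to first trimester BMI: BMI < 25, BMI 25–30 or BMI > 30". The Discussion (Continuous midwife support) counts this as a strength: "The women are also stratified according to BMI to minimize the risk of uneven randomization".

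Under Primary outcome, the first of two primary outcomes is "the rate of normal deliveries", a yes/no variable for each woman.

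Under Statistical analyses of data, the only test named for such a variable is "Differences between categorical variables will be analysed by Pearson chi-square test", with the threshold that P "values < 0.05 are considered statistically significant". Neither a stratified test nor a model with BMI appears, and no reason is given for leaving BMI out.

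The Power calculation section assumes 30% pathological births under standard support, a halving under proactive support, 80% power and 120 women per group. It gives no event rates by BMI class and no expected share of women in each class.

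**The concern.** Stratified randomisation with restricted allocation makes the arms alike on BMI. If BMI predicts the outcome, the difference in proportions then varies less from trial to trial than two unstratified samples would. The Pearson chi-square does not know this. Its variance still contains the between-class variation that the design has removed, so the P value is on average a little too large and the unadjusted interval a little too wide. The general remedy is to analyse by the factors used to randomise.

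The article's own reason for stratifying, that "because obesity influences almost all aspects of pregnancy and labour", is an argument for using BMI in the analysis as well. At stake is some precision that the design has already paid for. Control of the false-positive rate is not at stake.

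**Working it through.** **Inputs from the article.** Control risk 0.30, proactive risk 0.15, power 80%, 120 per arm (Power calculation); significance level 0.05 (Statistical analyses of data); three BMI classes (Assignment of interventions and collection). Sidedness is not stated; two-sided is used because it reproduces the sample size.

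**Assumptions, not in the article.** Per arm, 74, 31 and 15 women in the classes <25, 25–30 and >30 (about 62/26/12%), exactly balanced between arms. Control risks by class follow three gradients: weak 27/33/42%, middle 24/36/50%, strong 20/40/60%. Against BMI <25, these imply odds ratios for pathological birth of about 1.3 and 2.0, 1.8 and 3.2, and 2.7 and 6.0.

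**Step 1: reproduce the plan's figure.** The mean risk is 0.225, so

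n = [1.960 × √(2 × 0.225 × 0.775) + 0.842 × √(0.30 × 0.70 + 0.15 × 0.85)]² / 0.15² = [1.960 × 0.5906 + 0.842 × 0.5809]² / 0.0225 ≈ 120.5, or 121 per arm.

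The stated 120 is reproduced to within one woman; power at 120 per arm is 79.8%. A one-sided calculation would give 95. The sample size is thus an unstratified two-proportion calculation.

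**Step 2: how conservative is Pearson under the null?** Pearson uses a variance proportional to p̄(1 − p̄). With exact balance within strata, the true variance is proportional to Σ(n_k/n) p_k(1 − p_k). With R the ratio of true to assumed variance, the real two-sided error is 2 × [1 − Φ(1.960/√R)].

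| Control risks | p̄ | p̄(1 − p̄) | Within-strata | R | 1.960/√R | Type I error |
|---|---|---|---|---|---|---|
| 27/33/42% | 0.3043 | 0.2117 | 0.2091 | 0.988 | 1.972 | 4.9% |
| 24/36/50% | 0.3035 | 0.2114 | 0.2033 | 0.962 | 1.999 | 4.6% |
| 20/40/60% | 0.3017 | 0.2107 | 0.1907 | 0.905 | 2.060 | 3.9% |

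For the last row, the within-strata term is (74 × 0.16 + 31 × 0.24 + 15 × 0.24)/120 = 22.88/120 = 0.1907.

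Simulation (200,000 trials per scenario) agrees: 4.8%, 4.5% and 4.0% for Pearson, against about 5.0% for the BMI-stratified Cochran-Mantel-Haenszel (CMH) test.

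**Step 3: power.** The treatment effect can be set in two ways: apply the overall odds ratio (0.15/0.85)/(0.30/0.70) = 0.412 within each class, or choose the common odds ratio so that the overall proactive risk is exactly 15%.

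| Control risks | Effect set by | Pearson | CMH | Gain (points) |
|---|---|---|---|---|
| 27/33/42% | odds ratio 0.412 | – | – | about 0.1 |
| 24/36/50% | odds ratio 0.412 | 78.9% | 79.7% | 0.8 |
| 24/36/50% | proactive risk 15% | 82.5% | 83.1% | 0.6 |
| 20/40/60% | odds ratio 0.412 | 75.1% | 77.6% | 2.5 |
| 20/40/60% | proactive risk 15% | 82.3% | 84.4% | 2.1 |

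**Step 4: why some power figures fall below 80%.** With the strong gradient and odds ratio 0.412, the proactive risks by class are 9.3%, 21.5% and 38.2%. The overall risk is (74 × 0.0933 + 31 × 0.2154 + 15 × 0.3818)/120 = 16.1%, so the simulated difference is 30.2% − 16.1% = 14.1 points and not 15. Most of the fall to about 75% comes from that smaller effect. Only the gap between Pearson and CMH on the same row belongs to the choice of test.

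**Step 5: sensitivity to the assumptions.** A second set of simulations fixed the overall risks at exactly 30% and 15% and used class shares of 65/23/12% and 50/30/20%. Pearson power was 80.5% to 82.2% in every BMI scenario. The gain from CMH was about 0 points at BMI odds ratios of 1.25 and 1.5, about 0.2 at 1.5 and 2, 1.1 to 1.3 at 2 and 4, and 3.1 to 3.3 at the extreme 3 and 9.

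**Step 6: without restriction within strata.** If allocation within each class is a simple coin toss, Pearson's type I error in simulation is 4.91% to 4.98% for the three gradients of Step 2. The conservatism disappears.

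**The case against.** The strongest reply is that nothing is broken. An unadjusted test after stratified randomisation keeps its error rate at or below 5%, and the balance that the Discussion gives as the purpose of stratifying is achieved whichever test follows. That stands, and it limits the point to efficiency.

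Second, the article does not show that BMI predicts this outcome strongly. It speaks of obesity in general, the outcome is a composite, and women with insulin-treated diabetes, pre-eclampsia or conditions needing extra monitoring are excluded. This stands too: the size of the loss rests on assumed gradients, and with a weak one it is negligible.

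Third, the article says only that randomisation is computer-based and stratified. Block details may sit in the full protocol. So a reader might infer that the standard error is certainly too large, but that holds only if allocation is restricted within strata.

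Fourth, a reader might infer from the figures near 75% that ignoring the strata pulls the trial well below its planned power. Step 4 shows otherwise: with the planned 15% in the proactive arm, Pearson keeps about 82% in the same scenario.

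Fifth, an analysis plan that is not shown may adjust for BMI. This answers part of the point: the absence of BMI from the list of baseline variables is missing detail only. It does not answer the rest, because the article names a specific test for all categorical variables, and that is a stated choice.

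Finally, one might suspect that exclusions after randomisation have upset the BMI balance. Trial status lists such cases but gives no counts by BMI class, so this cannot be claimed.

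**Conclusion.** The point holds as a small inefficiency. The analysis stated for the primary binary outcome does not use the one factor on which randomisation is stratified. Given restricted allocation within strata and a prognostic BMI, the Pearson test runs at about 4.0% to 4.8% instead of 5% and gives up about 0.1 to 2.5 points of power across the three assumed gradients. A gradient more extreme than these would cost a little over 3 points. Without restriction the standard error is sound, though an adjusted analysis can still gain some precision.

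A reader might infer that the test is invalid, or that the trial is underpowered because of it. The documents support neither: false positives are not inflated, and at 30% versus 15% the Pearson test delivers about 80% or slightly more. The reason to change is that the improvement is free and follows from the article's own case for stratifying.

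**What to change.** State the primary analysis of normal delivery as a Cochran-Mantel-Haenszel test stratified by the three BMI classes used at randomisation. Report with it a stratified risk difference and its 95% confidence interval, for example Σw_k d_k / Σw_k, where d_k is the difference in proportions in class k and w_k = n_1k n_0k/(n_1k + n_0k). Logistic regression with arm and BMI stratum is an acceptable alternative; its odds ratio is conditional on BMI class, so the risk difference should still be reported. Include BMI stratum in the comparisons of the CEQ, duration of labour and the other outcomes. Keep the unadjusted Pearson chi-square as a supportive analysis.

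The cost is a few lines of text, settled before the outcome data are analysed. First-trimester BMI is already needed to randomise, the methods are available in the software that the article names, and the sample size need not change. If BMI turns out to be unrelated to the outcome, nothing material is lost: in simulation, CMH power was 80.4% against 80.5% for Pearson with class shares 65/23/12%.
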